## Methods and analysis

### Trial design

The THROS trial is a non-inferiority, multicentre, randomised controlled trial with two parallel groups: RBL vs. SCL. The allocation ratio is 1:1. Crossover is possible for patients who experience no improvement of symptoms after at least two treatments within one treatment arm. It is expected that when two treatments have not reduced symptoms and a third treatment is necessary, both patients and surgeons are inclined to try a new treatment option. So crossover rate is also indicative for treatment success. Also, when patients have a strong preference for one of the two treatment arms and refuse randomisation, then registration in the preference arm is allowed. All patients’ symptoms could not be effectively managed by conservative treatment, which included dietary changes, laxatives, and lifestyle improvements. Conservative management was the first step of therapy in all cases. After eligibility has been established and patients have given their written informed consent, allocation or registration to one of the two treatment arms is possible. Data will be analysed on both ‘intention to treat’ and ‘per protocol’ basis.

The trial was registered at the Dutch Trial Register (NL8377). The protocol was drafted in accordance with the Standard Protocol Items: Recommendations for Interventional Trials statements (SPIRIT) [12].

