### Sample size calculation

The sample size is based on a success percentage of 70% in both treatment arms, in terms of symptom reduction. Based on the available literature from Cocorullo et al. [6], we will perform a non-inferiority analysis with a two-sided significance (alpha 2.5%), 80% power and a 10% non-inferiority limit. Consequently, a total of 330 randomised patients are required per arm, so 660 randomised patients in total.Significance level (a) = 2.5%Power (1-beta) = 80%Non-inferiority limit = 10%Proportionality group A = 70%Proportionality group B = 70%Sample size required per group = 330Total sample size required = 660

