### Recruitment and blinding

In the Netherlands patients with HD are mostly referred to the surgeon by their general practitioner. The outpatient clinic nurses or researchers will screen for eligibility and send the patient written information (study information folder (PIF) and plan their appointment at the outpatient clinic. This allows for a minimum of 48 h to reflect on the information. The patient takes the information to the outpatient clinic appointment to discuss with the treating physician. In the case of participation, oral and written consent are gathered.The treating physician generates the allocation process or registration to the preference arm, after written informed consent has been provided.The randomization sequence will be computer generated with the Castor^EDC^ program (version 24.41) without stratification, with 1:1 allocation to either group, generating a unique record number.Both patient and treating physician are not blinded for the treatment arm.In concept, the researcher who completes the telephone interviews at 7 days and 6 months is blinded to the given therapy and is instructed not to actively ask patients which treatment they received. However, the data is added in the same database system, so complete blinding is not guaranteed. The physician at T = 0 and T = 6 weeks is not blinded as it is otherwise impossible to complete the treatment. Also, at 6 weeks the treating physician should repeat the initial treatment when necessary, following protocol.

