## Statistical analysis

Both intention-to-treat and per-protocol analyses shall be carried out. Crossover is not desirable, but possible if deemed necessary by the treating physician. Crossover will be considered as a secondary outcome measure. Analyses will be carried out using SPSS version 26.0. A *p*-value of 0.05 or less is considered as statistically significant.

For the primary outcome, any reduction in a PROM/PREM score per symptom is scored as ‘improvement’ when considering the results as binary success or not. Analysis of primary outcomes will be tested with chi-square test or Fisher’s exact test. Considering there are four time points for the outcomes, these time points will be taken into account during the analysis. Descriptive methods will be used to check the quality of the data, homogeneity of the two treatment groups and primary and secondary endpoints. Significant confounders will be identified using multivariate analysis. Categorical variables will be presented as percentages and continuous variables will be presented as means with their confidence intervals. To examine gender differences, an additional analysis will be carried out. An interim analysis will take place after the first 300 patients have been randomised and 6-month follow-up is completed. Both the number of patients who experienced complications and the number of patients with recurrent symptoms after 6 months will be evaluated between the two groups. If there are significant differences, then the entire study group will discuss these findings and discuss whether the study can be continued.

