### Data monitoring

The THROS trial is monitored internally by the Scientific Office of the Flevoziekenhuis in cooperation with the hospital quality and safety department. All participating centres also ensure monitoring standards. Any serious complications must be reported as soon as possible to the coordinating researchers who will report this to the chairman of the Scientific Office. No external data monitoring committee has been established because the interventions included in this trial are low-risk interventions and have been used in the participating centres for a significant amount of time (i.e. > 10 years). The principal investigator will update the Medical Ethics Committee on the status of the investigation once a year. An estimation of the degree to which the study objectives are reached, the reporting of adverse events, and other reports that may be relevant for the assessment of the investigation's progress are all included in the yearly progress report.

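### Interim arm comparisons of two primary outcomes go, once significant, to the entire study group, which would include the unblinded physicians who still allocate, treat and score patients

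*Protocol article*

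**What the plan says.** The Statistical analysis section plans one interim analysis, once the first 300 randomised patients have completed 6 months. It covers the number of patients with complications, and "the number of patients with recurrent symptoms after 6 months will be evaluated between the two groups". The consequence is stated as: "If there are significant differences, then the entire study group will discuss these findings and discuss whether the study can be continued". The same section sets significance at a p-value of 0.05 or less and gives no separate level for the interim.

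The Abstract, Objectives and Primary outcomes sections list both complications and recurrence as primary.

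On oversight, the Data monitoring section says: "No external data monitoring committee has been established". The reason given is that both treatments are low-risk and long in use. Monitoring is internal, by the Scientific Office of the coordinating hospital with its quality and safety department.

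On blinding, the Recruitment and blinding section says: "Both patient and treating physician are not blinded for the treatment arm". The treating physician runs the allocation or registers the patient to the preference arm. The telephone researchers at day 7 and 6 months are meant to be blinded, although the section concedes that this is not guaranteed.

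**The concern.** Recurrence at 6 months is an effectiveness outcome, so this look goes beyond safety monitoring. If it shows a significant difference, the comparison is opened to people who can still influence the remaining data. Four routes are visible in the protocol:

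- **Enrolment.** A physician who knows which arm is ahead can steer a patient away from randomisation, and the preference arm is a ready alternative.
- **Crossover.** The treating physician judges whether it is needed. It is a secondary outcome, and the Trial design section treats it as a sign of treatment success.
- **6-week scoring.** The symptom questionnaire, the incontinence score and the physical examination are completed at a clinic visit with an unblinded physician.
- **Telephone assessment.** If these researchers belong to the study group, disclosure weakens the only blinding in the trial. They collect the 6-month symptom scores and recurrence.

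A second issue is how easily the trigger is met. Two outcomes are compared, and the only level in the text is 0.05 for each. A chance finding could start a debate on ending the trial at less than half its planned size.

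**Working it through.** **Inputs from the protocol.** Interim at 300 patients; planned total 660 ("a total of 330 randomised patients are required per arm, so 660 randomised patients in total"); "The allocation ratio is 1:1"; two interim outcomes; general level 0.05. **Assumption.** The correlation between the two outcomes is not given, so 0 to 0.8 is shown.

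**1. The plan's own figure.** "The sample size is based on a success percentage of 70% in both treatment arms, in terms of symptom reduction", with a margin of 10% and 80% power. Per arm, n = (1.960 + 0.842)² × (2 × 0.7 × 0.3) / 0.10² = 329.7, so 330. This matches when 2.5% is one-sided. The text calls the 2.5% two-sided, which would need 400 per arm, so that label should be reconciled. The test that sizes the trial is therefore non-inferiority on symptom improvement, which the interim does not examine.

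**2. Information at the interim.** 300/660 = 0.4545. The correlation between interim and final statistics for one outcome is √0.4545 = 0.674.

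**3. Chance of a false trigger.** With no true difference, two outcomes at 0.05 each, and a bivariate normal for the two test statistics:

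| Correlation of outcomes | P(at least one significant) |
|---|---|
| 0 | 1 − 0.95² = 9.75% |
| 0.3 | 9.5% |
| 0.5 | 9.1% |
| 0.8 | 7.8% by integration (7.9% by simulation) |

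**4. Repeated testing of one outcome.** If recurrence, or complications, is tested at 0.05 at both looks and either result counts as a finding, P(|Z₁| > 1.96 or |Z₂| > 1.96) at correlation 0.674 is 8.46%, instead of 5%.

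**5. Effect of a strict interim level.** With interim p < 0.001 (|Z₁| > 3.29) and the final test at 1.96, the same calculation gives 5.03%.

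**6. Consequence of a stop.** With 150 per arm, the standard error of the difference is √(0.42/150) = 0.0529. Power for non-inferiority is Φ(0.10/0.0529 − 1.96) = Φ(−0.07), about 47%.

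**7. Price of p < 0.001 for complications.** As an illustration only, take true rates of 10% and 20% with 150 per arm. The standard error is √(2 × 0.15 × 0.85/150) = 0.0412 under the null and √((0.09 + 0.16)/150) = 0.0408 under the alternative. Detection at 0.05 is Φ((0.10 − 1.96 × 0.0412)/0.0408), about 68%. At 0.001 it is Φ((0.10 − 3.29 × 0.0412)/0.0408), about 19%.

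**The case against.** The strongest reply has five parts.

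- **No interim level is stated.** The 0.05 is the general threshold, and a full protocol or analysis plan may set a boundary. This stands. One cannot say the plan prescribes an unadjusted 0.05 at the interim, only that no other level is given. The outcomes, the trigger and the audience, however, are fixed in the article itself.
- **The trial's main error rate is untouched.** This also stands. A reader might infer that the interim inflates the type I error of the non-inferiority conclusion ("we will perform a non-inferiority analysis with a two-sided significance (alpha 2.5%), 80% power and a 10% non-inferiority limit"). It does not, because symptom improvement is not tested at that look and a significant interim is not a claim of success. A reader might also combine two outcomes and two looks into about 16%. That figure assumes independence, and 9.75 points of it would exist with the final look alone.
- **The rule is only a discussion.** Correct. The 8% to 10% is the chance of a false alarm. No stopping probability can be derived, because there is no stopping rule.
- **The study group is undefined and sees results only when they are significant.** It would be too strong to call it a group of unblinded recruiters, or to say the comparison is disclosed routinely. But the word entire leaves no ground for excluding the treating physicians, and a significant result is when knowledge is most likely to change behaviour. Recruitment may have passed 300 by then, so how much of the trial would be exposed is unknown.
- **Low-risk treatments need no external committee.** That is a reasoned choice about safety oversight. It does not address who should see comparative effectiveness results.

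**Conclusion.** The point holds mainly as one of disclosure. Followed as written, the plan would show significant arm differences in two primary outcomes to people who allocate, treat and score patients without blinding, and possibly to the telephone assessors. The size of the resulting bias cannot be calculated from the protocol.

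The statistical part is secondary. If 0.05 applies to each outcome, a trial with no true difference has an 8% to 10% chance of at least one trigger, over correlations from 0.8 down to 0. A recurrence or complication difference tested at 0.05 at both looks would carry about 8.5% error instead of 5%, but only if either look may count as a finding. The non-inferiority test on symptom improvement keeps its level.

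The sponsor should correct this, because the change is small and can be made before the interim takes place.

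**What to change.** In the Statistical analysis section, replace the sentence on discussion by the entire study group with text to this effect:

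> Arm-level interim results are prepared by and shown only to members of the internal monitoring body who do not recruit, treat or assess trial patients. That body passes a recommendation on continuing, without arm-level results, to the study group. The interim analysis supports no efficacy or non-inferiority claim. Recurrence is compared at a pre-stated strict level (for example p < 0.001). Complications are reviewed as safety monitoring at a separate pre-stated level.

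At p < 0.001 for recurrence, the final two-sided level for that outcome stays at about 5.03%, so its final test needs no practical adjustment. The same level should not be carried over to complications without thought, given the fall in detection from about 68% to 19% in the illustration.

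**Cost.** No new external committee is needed. The protocol does not say that the internal body is separate from recruitment, so suitable members, and someone outside the trial team to run the comparison, must be named. The study group gives up sight of the interim arm results, and moderate early recurrence differences will not prompt a discussion. Prompt reporting of serious complications under Data monitoring is unaffected.

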### Data monitoring

The THROS trial is monitored internally by the Scientific Office of the Flevoziekenhuis in cooperation with the hospital quality and safety department. All participating centres also ensure monitoring standards. Any serious complications must be reported as soon as possible to the coordinating researchers who will report this to the chairman of the Scientific Office. No external data monitoring committee has been established because the interventions included in this trial are low-risk interventions and have been used in the participating centres for a significant amount of time (i.e. > 10 years). The principal investigator will update the Medical Ethics Committee on the status of the investigation once a year. An estimation of the degree to which the study objectives are reached, the reporting of adverse events, and other reports that may be relevant for the assessment of the investigation's progress are all included in the yearly progress report.

## Ethics and dissemination

### Ethics approval

This trial will be carried out according to the principles of the Declaration of Helsinki (Fortaleza October 2013) and in accordance with the WMO and other European guidelines, regulations and acts such as the GDPR (General Data Protection Regulation) and Good Clinical Practice (GCP). The medical ethics committee approved the protocol of this study on September 24, 2020 (nr. 2020_053). Important modifications from amendments will be communicated to participating centres.

### Consent procedure

The allocation process and consent procedure are described above. Moreover, participation is voluntary and patients are free to discontinue participation and withdraw from the study at any time without giving reason. On the consent form, participants will be asked if they agree to the use of their data should they choose to withdraw from the trial. Participants will also be asked for permission for the research team to share relevant data with people from the centres taking part in the research or from regulatory authorities, where relevant. On the consent form, we also request participants' consent to contact them for ancillary studies.

### Risk of harms

No additional harm or compensation is predicted for trial participation since both treatment choices are part of approved clinical practice for HD. However, of course, the principal investigator and his team will report all serious adverse events (SAEs) to the accredited medical ethical committee. In addition, once a year throughout the trial, the study group will submit a safety report to the accredited MEC.

### Confidentiality/access to data

After allocation to one of the treatment arms within Castor^EDC^ an unique record number is regenerated. Original data and the decoding key will be stored at the patients’ clinic and must be handled with care. The data will be saved for 15 years and only members from the research group will have access to the study data. The final trial data for this protocol can be provided upon reasonable request.

### Methods of dissemination of results

Results from this study will be communicated through peer-reviewed medical journals and data can be made available upon reasonable request.

## Discussion

The THROS study is the first large multicentre randomised trial to study the difference in effectivity between RBL and SCL for the treatment of grade 1–2 HD. Primary and secondary outcomes consist of both objective and subjective patient-reported outcomes. In this non-inferiority trial, we hypothesize that SCL is non-inferior to RBL with regard to effectiveness, patient experience, complications and recurrences.

As HD is one of the most common conditions in the general population, with an annual incidence of 5%, it represents a significant epidemiologic and economic burden. Most patients experience blood loss and for some patients, this blood loss can cause symptomatic anaemia. Patients with grade 1–2 haemorrhoids may also experience other symptoms like itchiness, pain or soiling and, because of additional stigma and shame, it represents a high burden that affects the quality of life.

However, patients’ experience of HD symptoms and its burden on everyday life is in contrast with the surgeon’s experience in which it is perceived as a ‘simple’ diagnosis with a relatively ‘simple’ solution/treatment. Therefore, surgeons and proctologists are driven to treat their patients with less invasive, but most effective method, in which the patients’ experience of the treatment also plays an important role. This is especially so considering that for the majority of cases, a singular treatment is insufficient to fully treat the HD.

In case of more severe (grade 3–4) or recurrent HD, there are several multicentre randomised controlled trials studying the effect of different treatment options. Both the HollAND and Napoleon trial, which were forced to stop prematurely due to inclusion difficulties, are currently in the follow-up phase. Both studies compare more invasive techniques (haemorrhoidectomy or sutured mucopexy) with RBL [14, 15]. However, symptomatic grade 1–2 HD are far more common in the general population and so an answer as to what the best and most appropriate minimal invasive treatment option is, is needed.

For the treatment of grade 1–2 HD, there are several options described in the literature and some of them are relatively new [16–19]. The THROS trial focuses on two less invasive treatment methods and it will provide us with information as to which commonly used treatment method (RBL or SCL) of grade 1–2 HD is the most effective, gives fewer complications and is experienced by the patient as the best option. Considering the available literature on SCL and RBL, we expect the efficacy and complication rates to be equal. However, in most cases of SCL or RBL therapy, repeated procedures are necessary to achieve acceptable symptom reduction, and it is for that reason that it is very important to investigate the patients’ experience of treatment. In current literature, there is limited available evidence regarding patient experience, except for pain scores [6]. Therefore, it is of even greater importance to compare both treatments in other domains, with the use of the recently developed PROM-HISS questionnaire [11, 13].

## Appendix

Patient-reported experience measure (PREM):

1. How much pain did you experience DURING the treatment on a scale of 0 (none) to 4 (very much)?: 0–4
2. How much pain did you experience AFTER the treatment?: 0–4
3. How much feeling of URGE did you experience AFTER the treatment?: 0–4
4. How satisfied were with the treatment on a scale of 1 (very satisfied) to 5 (very unsatisfied)?: 1-5
5. Would you, if necessary, undergo this treatment again?: yes/no
6. Would you recommend this treatment to acquaintances with the same symptoms?: yes/no
